### Strategies to improve adherence to interventions {11c}

MTX is considered as a chemotherapy medication (despite the low dose of the tablets of 2.5 mg each), and therefore, it is not allowed for researches to count tablets at the moment of tablet distribution and return, according to our pharmacy guidelines. Therefore, participants will be asked to complete a medication diary in order to monitor medication adherence, which will be done for study medication and concomitant non-steroidal anti-inflammatory drugs (NSAIDs) use (and will be reviewed every visit).

### Relevant concomitant care permitted or prohibited during the trial {11d}

#### Concomitant and prohibited treatment

Concomitant treatment with analgesics such as acetaminophen and/or NSAIDs will be allowed for all participants, except 24 h before MRI scans [40]. Treatment with DMARDs (conventional synthetic, biologic DMARDs, or jak-stat inhibitors) or corticosteroids (systemic or intra-articular) will be prohibited during the trial, unless participants reached the primary endpoint of the trial. Also, any other medicinal products that, in the supervising physician’s opinion, may influence underlying disease activity through effects on immune or inflammatory responses, or both, are prohibited (with the exception of NSAIDs and acetaminophen).

All participants will be evaluated for safety. Screening on toxicity on MTX will be performed by the treating rheumatologists in line with the Dutch guidelines on MTX as recommended by the Dutch Society for Rheumatology (https://www.nvr.nl/richtlijnen/nvr-richtlijnen-standpunten-en-zorgpaden/).

#### Concomitant care

Study visits will be scheduled every 4 months for 2 years follow-up; however, in case a participant has an increase in symptoms in between two study visits, he/she can be seen for an additional visit by their rheumatologist (Fig. 2). In case clinically apparent inflammatory arthritis is detected, an additional study visit will take place after 2 weeks (and in between the already scheduled study visits), to check if a participant has reached the primary endpoint, which is solely based on physical joint examination. Except for MRI positivity/negativity during screening, MRI results during the trial will not be communicated to participants and rheumatologists. Ultrasound will not be made. Hence, evaluation of the primary endpoint is not influenced by the results from imaging.

### Provisions for post-trial care {30}

Participants who reach the primary endpoint may proceed to open-label DMARD therapy, which will be prescribed by their rheumatologist, and followed through routine clinical practice. After these first 2 years, the RCT will be stopped (and unblinded) and participants will be followed for another 3 years under observational extension based on regular care (Fig. 2). During this period, participants who have not achieved the primary endpoint at month 24 can remain under rheumatologic follow-up. This will be left to the decision of the treating rheumatologists and participant (shared decision-making healthcare). If routine follow-up at the rheumatology outpatient clinic is then stopped, participants will be provided with the contact details of the research team to ensure prompt reporting of new signs and symptoms of inflammatory arthritis. In addition, at month 60, all participants will be contacted again.

All patients are insured during the trial or when an injury (as a consequence of the trial) originates within 4 years after the trial.

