### Who will be blinded {17a} and procedure for unblinding if needed {17b}

All scientific staff, rheumatologists, research nurses, and participants will remain blind to the treatment allocation. Unblinding will occur if medically necessary. In case the primary endpoint is met, participants will be treated with open-label DMARD therapy according to the routine care and the medication choice is left to the decision of the treating rheumatologist. No unblinding will take place at this time. In case participants will stop the study medication because of side effects at an earlier point in time than the 12-month period, unblinding will not take place as well (in order to prevent expectation bias influencing the treating physicians). The data safety monitoring board (DSMB) receives information blinded to the treatment allocation; however, if required for safety issues, the board can ask the pharmacist to provide them with unblinded data. Otherwise, unblinding will take place when the last study visit after 2 years of follow-up of the last included participant is done, and data quality checks (QCs), as described in the “Data management {19} and confidentiality {27}” section, are performed.

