### Plans to promote participant retention and complete follow-up {18b}

The intention is to follow all participants for a total period of 24 months of the RCT at the LUMC. Participants who need to stop the study medication because of toxicity (or other reasons, e.g., wish of participant) will remain in the trial for the entire follow-up period. In case a participant finds the trial too demanding, we will ask if an adjusted scheme is an option, which will at least include the last visit at the LUMC at 24 months, and if also possible the 12-month visit.

Participants who will reach the primary endpoint will be treated by their rheumatologist according to the Dutch and international guidelines. Participants who reach the primary endpoint will be asked to complete the questionnaires at month 24.

Amendment (Protocol version 7, 25-02-2020) includes the collection of observation data between 24 and 60 months and questionnaires completed by the participants at 5 years of follow-up. All included participants will be contacted 5 years after the inclusion in the cohort to complete the questionnaires at month 60. Data from the disease course between months 24 and 60 will be retrieved from the medical files if participants consent with the observational extension study. This extension phase is submitted to and approved by the medical ethical testing committee (METC) in 2020, partly in response to comments of patient partners that suggested to determine if differences between the groups will be sustainable in the long term.

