The follow-up duration of 24 months seems sufficient for the assessment for the primary endpoint, because our present data suggest that the majority of CSA patients who convert to clinically detectable arthritis and RA do so within 4–6 months [14]. The follow-up includes 12 months without study medication. Supposed that MTX would postpone but not prevent the development of RA, a medication-free period of 12 months should be sufficient to detect this. Also, in the PROMPT trial, only two patients developed RA later than 12 months after cessation of study medication [48]. Nonetheless, the most recently approved amendment to the protocol (approved February 2020, protocol version 7) includes an observational extension of the trial with a total follow-up time of 5 years, as the achievement of an outcome after a relatively short time period of time is not reflective of the subsequent disease course [49]. A long-term follow-up is required to evaluate whether results are sustainable and valuable. Especially, patients have indicated that the current disease burden is mostly caused by pain, fatigue, and functional impairments [50]; the decision to extend the follow-up duration is therefore in line with the suggestions of patient partners. After 5 years follow-up, we will assess primary and secondary endpoints, to evaluate if differences are permanent in the longer term.

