The primary endpoint can be considered as the main outcome assessed from the perspective of rheumatologists, but patients indicated that the burden of RA is best expressed by assessing the domains of independence (functioning, workability), pain, and fatigue [50]. The secondary endpoints may therefore be considered as the benefit from very early treatment from patients’ perspectives. Moreover, an evaluation 1 year after the cessation of study medication may be insufficient to determine if favorable effects are sustainable over time [49]. Thus, as PROs are considered most valuable by patients, and as the 2 years measurement insufficiently assesses sustainability, all secondary endpoints will also be analyzed again 5 years after the study start.

This trial was designed in 2014, and risk stratification was based on the first 120 included Leiden-CSA patients, which resulted in a risk of 35% to progress to RA during the next year (PPV) in patients with CSA and a positive MRI. Based on these numbers, a sample size of 230 participants was required for a well-powered study. Recently, it was observed that higher PPVs can be obtained when weighting tenosynovitis (particularly, MCP extensor peritendinitis) and the number of locations with subclinical inflammation (PPVs up to 63–67%) [17]. This creates opportunities for (subgroup) analyses on participants with high-risk characteristics.

CSA patients will be enrolled in this trial irrespective of the auto-antibody status as it has been reported that with current treatment strategies, the disease burden is similar in ACPA-positive and ACPA-negative RA patients [19], and in addition, EULAR recommendations for the management of early arthritis recommend MTX as the first-line therapy, independent of the auto-antibody status [20]. Nevertheless, there is accumulating evidence that ACPA-positive and ACPA-negative RA have different etiopathologies, as underlying genetic [51] and environmental risk factors differ [52, 53]. Also, subtle differences in symptoms [54] and timelines of the symptomatic phase that precedes the development of clinical arthritis have been reported [55]. It is therefore possible that disease maturation in the symptomatic pre-arthritis phase differs between the two groups. Consequently, the influence of treatment may be different in APCA-positive and ACPA-negative CSA. In addition to adding an adjustment factor, this can be addressed by stratifying the analyses for ACPA.

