## Trial status and other additional information

The TREAT EARLIER study trial received ethical approval on 2 March 2015 (Protocol version 2, 12-01-2015). The trial is registered at Dutch Trial Register (NTR4853/Trial NL4599, https://www.trialregister.nl/trial/4599); 20 October 2014.

The first participant was randomly assigned in April 2015. The RCT is expected to end in September 2021.
Trial-start: Protocol version 1 (20-10-2014) changes were required, and version 2 (12-01-2015) was approved.First amendment. Increase samples from 200 to 230 due to expected larger dropout rate than included in first sample size calculation (20% versus 10%): protocol version 3 (26-03-2018) changes were required, and version 4 (31-05-2018) was approved.Second amendment. Deviation of MRI scan as the MRI scanner that is used from 2015 onwards is expected to be technically “end-of-life” by December 2019: protocol version 5 (18-01-2019) was approved. Up to 30 participants will be scanned on 1.5-T and 3-T MRI.Third amendment includes a collection of observational data between 24 and 60 months: protocol version 6 (03-02-2020) changes were required, and version 7 (25-02-2020) was approved.

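### The 5-year results are meant to show whether differences are permanent, but the follow-up stated after month 24 cannot re-assess the primary or co-primary endpoint as defined, and part of it is unblinded

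*Protocol article*

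**What the plan says.** The aim of the extension is set in the Discussion: "After 5 years follow-up, we will assess primary and secondary endpoints, to evaluate if differences are permanent in the longer term". The same section adds that "all secondary endpoints will also be analyzed again 5 years after the study start", on the ground that the 2-year measurement does not settle sustainability.

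The conduct of the extension is described elsewhere:

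- **Provisions for post-trial care {30}:** "After these first 2 years, the RCT will be stopped (and unblinded) and participants will be followed for another 3 years", as an observational phase under regular care. For participants without the endpoint at month 24, on remaining under rheumatology follow-up: "This will be left to the decision of the treating rheumatologists and participant". Those who leave follow-up are given the research team's contact details, and everyone is contacted at month 60.
- **Plans to promote participant retention and complete follow-up {18b}:** "Data from the disease course between months 24 and 60 will be retrieved from the medical files", for those who consent to the extension. Questionnaires are completed at month 60.
- **Who will be blinded {17a} and procedure for unblinding {17b}:** apart from medical or safety need, "unblinding will take place when the last study visit after 2 years of follow-up of the last included participant is done" and the data quality checks have been performed. Data management {19} adds that the database is locked first.

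**The concern.** The endpoint definitions depend on examination. The primary endpoint is swelling found at physical examination that persists for 2 weeks. DMARD-free status requires a joint examination without synovitis and no DMARD use. If neither is examined on a schedule after month 24, a 5-year figure under the same name measures something else, namely arthritis that came to a clinician's attention and was written down.

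Detection can also become arm-dependent once allocation is known. Knowledge of having had active treatment or placebo may affect who stays under follow-up, whether doubtful swelling is recorded, when a DMARD is started under regular care, and how pain, fatigue and function are scored at month 60. The protocol recognises this risk during the trial: it withholds unblinding from participants who stop medication early, to avoid expectation bias in the physicians.

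At stake is how strongly a lasting difference, or its absence, can be attributed to disease modification.

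**Working it through.** **1. Endpoint procedures, before and after month 24**

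| Element | Months 0–24 | Months 24–60 as stated |
|---|---|---|
| Scheduled joint examination | every 4 months (Concomitant care) | none; follow-up optional |
| Persistence check | extra visit after 2 weeks (Plans for assessment {18a}) | none stated |
| Observers of swelling | two independent rheumatologists (Discussion) | not stated |
| Endpoint window | 2 years (Outcomes {12}) | no extended definition stated |
| DMARD-free status | joint examination at 2 years (Outcomes {12}) | no month-60 examination stated |
| Patient-reported outcomes | every visit | questionnaires at month 60 |

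Only the last row can be repeated as it stands. The rest becomes a file-derived outcome.

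**2. How much of the extension is open**

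The article gives no figure for this, so there is none to reproduce. The inputs come from Trial status: "The first participant was randomly assigned in April 2015. The RCT is expected to end in September 2021". Subtracting 24 months puts the last inclusion at about September 2019, which is 53 months after April 2015. Uniform accrual is an assumption, and the time needed for checks and database lock is ignored.

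For a participant enrolled at month t, blinded extension months = min(36, 53 − t).

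- Month 60 reached before unblinding requires t ≤ 53 − 36 = 17. That is 17/53 = 32% of participants, so about 68% answer the month-60 questionnaires after unblinding.
- Mean blinded extension time = (17 × 36 + 36 × 18)/53 = 1260/53 = 23.8 months, where 18 is the average over t = 17 to 53. This is 23.8/36 = 66%.
- Open time is 36 − 23.8 = 12.2 months on average, about 34%. Within the 68% it averages 18 months.

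Sensitivity: with 48 to 56 months of enrolment and accrual ranging from linearly rising to linearly falling, the blinded share of extension time runs from 44% to 86%. The share reaching month 60 while blinded runs from 6% to 59%.

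**3. What unequal detection could do (illustration only)**

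Observed 5-year risk = p + (1 − p) × q × s, where p is the 2-year risk, q the late-event risk among event-free participants and s the share of late events detected. The 2-year risks of 35% and 17.5% are the design assumptions under Sample size {14}. The values of q and s are not in the documents.

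Example with q = 10% and detection of 90% (placebo) and 70% (active):

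- Observed: 0.35 + 0.65 × 0.10 × 0.90 = 0.4085 and 0.175 + 0.825 × 0.10 × 0.70 = 0.2328; difference 0.176.
- True: 0.415 and 0.2575; difference 0.1575.
- Overstatement: about 1.8 percentage points.

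With q from 5% to 15% and active-arm detection of 50% to 70%, the overstatement is about 1 to 5 points. With 35% in both arms at 2 years it is about 1 to 4 points. With detection reversed (70% placebo, 90% active), the difference is understated by about 1 to 2 points. These figures apply the unequal detection to all late events, so they are high for an extension that is open only in part.

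**The case against.** The strongest reply is that the extension is openly called observational, was added by amendment in 2020 partly at the suggestion of patient partners, and carries no confirmatory test. The event definition for this phase and any masked abstraction may stand in the full protocol or the analysis plan, which are not shown. Most conversions are expected within 4 to 6 months, so late events may be few. Contact details for those who leave follow-up, and contact with everyone at month 60, reduce missed cases.

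Much of this stands. It limits the size of the problem, and the absence of abstraction detail from a condensed article is not itself a fault. What remains is that the article fixes both the 5-year aim and the data sources, and the two do not match for the examination-based endpoints.

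Three stronger readings are tempting but not supported:

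- **The 5-year question rests wholly on unblinded people.** A reader might infer this from the post-trial care section, which taken per participant would leave all 36 months open. That sentence speaks of the trial being unblinded, and the blinding and data management sections tie unblinding to the last participant and the database lock. The difference is mostly loose wording. Events in years 0 to 2, which carry into any cumulative 5-year result, are ascertained blinded.
- **The extension is the only test of sustainability.** The trial already has 12 blinded months off study medication with 4-monthly examinations. The extension is the only test beyond month 24.
- **No 5-year endpoint can be assessed.** The HAQ-DI, work and symptom questionnaires can be repeated.

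**Conclusion.** The point holds in a limited form. The follow-up stated for months 24 to 60 does not deliver the 5-year assessment of the primary endpoint and DMARD-free status that the Discussion announces; this follows from the text and needs no assumption. Arm-dependent ascertainment is possible after unblinding. Under the blinding section's rule and uniform accrual, that covers about one third of extension time (14% to 56% across the accrual patterns tried), and about 68% of month-60 questionnaires (41% to 94%) would be answered after unblinding. That individual allocations then reach participants and treating rheumatologists is an inference, since the article does not say how or when they are told. The direction and size of any bias cannot be derived from the documents. The primary, co-primary and gate-keeping analyses at 2 years are untouched; the issue is how strongly permanence may be claimed.

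**What to change.** 1. **Discussion:** call the 5-year arthritis and DMARD-free results exploratory, file-derived outcomes, distinct from the primary and co-primary endpoints, and limit the permanence claim accordingly.
2. **Extension data:** have existing staff without access to allocation abstract month 24–60 events under one fixed rule, and report results separately for blinded and unblinded person-time.
3. **Provisions for post-trial care {30}:** align the unblinding sentence with the blinding and data management sections, so that unblinding follows the last participant's month-24 visit and database lock.

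The cost is amendment wording and a masked abstraction list, with no extra visits. These steps do not remove optional follow-up or dependence on what the files record, which is why the relabelling is needed.

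Optional: do not routinely disclose individual allocations before that participant's month-60 questionnaire, keeping the existing provision for medical need. This would protect the patient-reported outcomes, but some participants would learn their allocation up to 3 years later. The trade-off is debatable, and the main recommendation does not depend on it.

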### Methods: outcomes {12}

The key primary endpoint is the development of clinically detectable arthritis, either fulfilling the 2010 criteria for RA [22] or unclassified clinical arthritis with SJC-66 of ≥ 2 joints, which persists for at least 2 weeks. This primary endpoint (incidence) will be obtained during a 2-year follow-up.

The presence of clinical arthritis (swollen joints) is based on the physical evaluation of the joints by rheumatologists. In case of doubt on the presence of arthritis, it will not be scored. At the start of the trial, all treating rheumatologists attended a session to verify the comparability of determining the endpoint. They demonstrated to have a high interindividual agreement in the evaluation of the presence or absence of clinical arthritis at the patient level. The primary endpoint is not influenced by results from imaging. Ultrasound will not be done. MRIs made during the trial will be stored under a randomization number, and the results will not be reported back to participants or rheumatologists. Thus, also the MRI results are not included in the decision making on the clinical endpoint.

The co-primary endpoint is DMARD-free status. This is assessed at the 2-year follow-up time point and is defined as the absence of clinically detectable synovitis at the joint examination in the absence of DMARD use (including systemic or intra-articular glucocorticoids).

A key secondary endpoint is functioning (Health Assessment Questionnaire Disability Index (HAQ-DI) range 0–3); this will be assessed together with other patient-reported outcomes (PROs) that are interrelated but for which no composite measure exists:
Work productivity and impairment scale (WPAI) (per item percentage/number and numeric rating scale (NRS) range 0–10).Symptoms: pain (NRS range 0–10), fatigue (NRS range 0–10), and morning stiffness (NRS range 0–10, duration in minutes).

Explorative endpoints:
Tender joint count (TJC-68, range 0–68).Hand function: ability to make a fist (left and right, yes/no), squeeze test (hand, foot, left and right, positive/negative), and grip strength test with a dynamometer (range 0–90).Global assessment (NRS range 0–10).Quality of life: short form-36 (SF-36) (range 0–100), EuroQol 5D-5level (EQ-5D-5L) (per item, range 1–5, and visual analog scale (VAS) range 0–100).Health appraisal: Brief Illness Perception Questionnaire short (B-IPQ) (per item, range 0–10), Rheumatology Attitudes Index (RAI) helplessness subscale (range 5–25).Cost-efficacy measurement by iMTA.Radiographic damage of the hands and feet, Sharp-van der Heijde scores (range 0–448).MRI-detected subclinical inflammation on the unilateral hand and foot, assessed semi-quantitatively using the RAMRIS score, evaluating synovitis (range per joint 0–3), BME (also called osteitis, range per bone 0–3), tenosynovitis (range per tendon sheath 0–3), and erosions (range per bone 0–10) [27, 28]. MRI scoring will be done with known time order and blind to any clinical data. The scores of synovitis, BME, and tenosynovitis are summed as the total MRI inflammation score (variable on the patient level). Total scores will be normalized as described by Sundin et al. [41]. Furthermore, the MRI data are categorized as “positive” and “negative” at the joint/location level and at the patient level. In addition, MRI data obtained during follow-up will also be categorized as “positive” and “negative” at the joint/location level and subsequently at the patient level. Categorization in positive/negative will be done with MRI data of symptom-free persons as a reference [13], similar to the methodology used at inclusion.Immunological exploratory endpoints: signatures of immune responses (such as the presence/absence of ACPA and RF, characteristics of the ACPA response, and other post-translational modifications such as anti-carbamylated protein antibodies), levels of acute-phase reactants (erythrocyte sedimentation rate, CRP), and inflammatory responses as defined through the analysis of serum and peripheral blood cell subsets (RNA expression profiling) and proteomics.(Serious) adverse events ((S) AEs).

